### 5.2 First Per Protocol population (PP1)

The population PP1 will be composed of subjects of the ITT population for whom:

- all the criteria for inclusion and exclusion are respected (not included wrongly);
- the intervention was carried out for the subjects of the intervention group (subject's file discussed during the first MDTM);
- 

### 5.3 Second Per Protocol population (PP2)

The population PP2 will be composed of subjects of the ITT population for whom:

- all the criteria for inclusion and exclusion are respected (not included wrongly);
- the 2 interventions were carried out for the subjects of the intervention group (subject's file discussed during the 1st and 2nd MDTM);

## 6 STATISTICAL ANALYZES

### 6.1 Principal analysis of the primary endpoint

The number and percentage of subjects who had at least one admission to a hospital ED in a one-year follow-up period will first be described by randomization group of the patient's NH (intervention or control) and in total.

The 1-year follow-up period for each subject begins at the end of the wave of inclusion in the center (i.e. start date of hospitalization collection).

The primary analysis of the effectiveness of management will compare the ED transfer rate between the two groups after a 1-year follow-up. To account for intra-center correlation (i.e., non-independence between observations of the same center) the effect of the intervention will be tested using a logistic regression model with random effects. The center randomization group (i.e. NH) subjects will be considered as a fixed effect and the center as a random effect

|                    |                                                                   |                                                                                                            |
|--------------------|-------------------------------------------------------------------|------------------------------------------------------------------------------------------------------------|
| Principal analysis | Statistical Analysis Plan (SAP)-IDEM Study 0910701
Version 1.0 | [figure not shown]
Hôpitaux de Toulouse |
|                    |                                                                   | 07/22/2016                                                                                                 |

to model the risk of a transfer to the ED. The risk of the first species for this main analysis is set at 5% (confirmatory test).

The intra-class correlation coefficient will also be calculated from this model.

Population of analysis: The main analysis of the primary efficacy endpoint of the intervention will be carried out on the subjects of the ITT population. Thus, subjects who left the study before 1 year of follow-up will still be considered in this analysis if their follow-up is at least 1 month. For example, a patient who died after 4 months of follow-up without ED transfer will have a primary endpoint equal to "No". This will lead to a possible underestimation of the rates of subjects admitted to ED in 1 year in the 2 groups but should not bias the comparison between the groups since the follow-up times should be close between the 2 groups.

As sensitivity analyzes, this analysis will also be performed on the PP1 population in addition to the ITT analysis.

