#### RESEARCH PROCESSES

The project is based on the REHPA network (Research in NH), set up in 2008 by our team and regrouping 240 NH with the aim of setting up clinical research projects specifically adapted to NH population. The cluster randomization takes into account some characteristics of NH related to the type of institution and the type of residents.

After being trained, the coordinating physicians practicing in the NH of the intervention group carry out a comprehensive geriatric assessment for each participating resident. The results of the various

|                    |                                                                   |                                                                                                                   |
|--------------------|-------------------------------------------------------------------|-------------------------------------------------------------------------------------------------------------------|
| Principal analysis | Statistical Analysis Plan (SAP)-IDEM Study 0910701
Version 1.0 | [figure not shown]
Hôpitaux de Toulouse |
|                    |                                                                   | 07/22/2016                                                                                                        |

tests are discussed between the coordinating physician and an expert from a nearby “memory resource and research center (MRRC)” or a “memory clinic (MC)” during a MDTM on Alzheimer's disease and related diseases.

Information on hospitalizations, drug and non-drug prescriptions, the appropriateness of hospitalization, the prevalence of psycho-behavioral disorders, residents' dependence and quality of life, the burden of the NH staff, the planning of advance directives and the overall cost of care are collected during follow-up. These monitoring data are collected by an ARC via a secure website (REHPA web page), or if necessary by mail or phone calls. The overall cost of care is provided by the French National Health Insurance Fund.

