### 3.3 Calculation of the number of subjects

The number of subjects required to meet our main objective was calculated by assuming a bilateral test with an alpha risk of 5% and a beta risk of 20% (80% power). On the basis of REHPA survey data (Rolland Y et al. 2009), 13.5% of all residents reported in the REHPA survey were admitted to hospital services in 3 months, an estimate of 54% in 1 year. By limiting the population of the REHPA survey to subjects with the inclusion criteria defined in IDEM, 12% were admitted to hospital services in 3 months, an estimate of 48% at 1 year. According to the same survey, of the 48% of all hospitalizations, half were via ED. Indeed, we can estimate an incidence of ED transfers of 24% at 1 year in the non-intervention group. Assuming a 30% reduction in the ED transfer rate in the intervention group, the 12-month ED transfer rate will be 16.8%. 516 subjects are needed in groups, taking into account the cluster effect with an ICC set at 0.02 of an attrition rate of 20% (average known % of deaths per year from REHPA data), the minimum number of subjects per group varies from 950 to 1050 depending on the inflation factor linked to the contamination between the groups, which has been varied from 5 to 10%.

|                    |                                                                   |                                                                                                            |
|--------------------|-------------------------------------------------------------------|------------------------------------------------------------------------------------------------------------|
| Principal analysis | Statistical Analysis Plan (SAP)-IDEM Study 0910701
Version 1.0 | [figure not shown]
Hôpitaux de Toulouse |
|                    |                                                                   | 07/22/2016                                                                                                 |

In total, 1,000 residents per group or 2,000 residents must be included. Taking into account an inclusion number of 30 residents on average per NH, 35 institutions per arm are necessary. Given the potential of 240 NH of REHPA network, this number of institution is realistic to achieve. In total 89 nursing homes have volunteered.

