### 6.3.7 The residents' quality of life

The total score obtained by the QOL-AD scale at the end-of-study visit will be compared between the 2 groups using a mixed model of analysis of variance (comparison of mean values). The randomization group will be considered as a fixed effect and the center as a random effect.

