### 6.5.3 Description of data collected at inclusion

The characteristics found in the randomized NH centers (randomization stratification factors, number of residents included) will first be described.

The following characteristics of the subjects identified for inclusion in the study will be described for the entire analysis population and will be described in the 2 groups (intervention, control):

- Criteria for inclusion and non-inclusion;
- Sociodemographic characteristics (age, sex, marital status, education, mother tongue (French yes / no), occupation (yes / no), seniority in the NH (in months);
- Medical history and associated pathologies (visual or auditory impairment, smoking and alcohol consumption, total Charlson Comorbidity Index score);

|                    |                                                                   |                                                                                                            |
|--------------------|-------------------------------------------------------------------|------------------------------------------------------------------------------------------------------------|
| Principal analysis | Statistical Analysis Plan (SAP)-IDEM Study 0910701
Version 1.0 | [figure not shown]
Hôpitaux de Toulouse |
|                    |                                                                   | 07/22/2016                                                                                                 |

- Cognitive antecedents (progressive decline yes / no, MMSE test yes / no and score, cognitive assessments yes / no and type of assessment);
- Family history of dementia (presence of family history of dementia yes / no);
- Hospitalizations during the last 3 months by type of hospitalization (planned or in emergency) and by type of service;
- Ongoing drug and non-drug treatments at inclusion by type of treatment;
- Anticipated prescriptions by type;
- GIR total score at inclusion.

The following results from the Comprehensive Geriatric Assessment (CGA) obtained during the inclusion visit only for the intervention group, will be described:

- Overall MMSE score;
- Results of the clock test (score and normality);
- Results of the Borson Mini-Cog (normality);
- Overall score of the 5 word test;
- Categorical verbal fluency test results (total words generated, total acceptable words);
- Confusion Assessment Method (CAM) test result (acute confusional state yes / no);

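### Nursing homes were randomised with stratification factors, but the confirmatory model omits them, so the test is conservative and loses a few points of power if the factors are prognostic

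*SAP*

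**What the plan says.** - **Randomisation.** The summary (Research processes) states: "The cluster randomization takes into account some characteristics of NH related to the type of institution and the type of residents". SAP 6.5.3 confirms that these are formal strata and gives them a descriptive role: "The characteristics found in the randomized NH centers (randomization stratification factors, number of residents included) will first be described". The SAP does not list the factors. That detail may sit in the protocol and is not criticised here.
- **Confirmatory model (6.1).** A random-effects logistic regression, tested at 5%: "The center randomization group (i.e. NH) subjects will be considered as a fixed effect and the center as a random effect". There are no other terms.
- **Adjusted model (6.2).** An exploratory second model adds five resident-level covariates: age, Charlson index, GIR, psychiatric history and cognitive decline at inclusion. No stratification factor is among them.
- **Secondary and additional models (6.3, 6.4).** The mixed models are specified with arm and centre (6.4 names no further term). The exception is the GIR change, which is also adjusted for the inclusion score. On quality of life, for example: "The total score obtained by the QOL-AD scale at the end-of-study visit will be compared between the 2 groups", with no covariate. NPI and IADL are handled in the same way.
- **Subgroups (6.7).** Presence of an Alzheimer's unit, and public or private status, enter the principal model only to test interactions. The SAP does not say whether these are the stratification factors.

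**The concern.** When clusters are allocated within strata, the arms are balanced on the strata by design. The sampling variance of the arm contrast then excludes the between-NH variance that the strata explain. A model with arm and centre only leaves that variance in the random centre term, so the reported standard error belongs to an unstratified design. The single confirmatory test is then run below its nominal 5% and the confidence interval is wider than the design warrants. With about 70 NHs, the between-NH component is a material part of the variance: at the planned ICC and cluster size it adds 58%. An SAP is where model terms are fixed, so this is not a matter left to the protocol.

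**Working it through.** **Inputs (SAP 3.3).** Control rate 24% ("we can estimate an incidence of ED transfers of 24% at 1 year in the non-intervention group"), intervention rate 16.8%, two-sided 5%, 80% power, ICC 0.02, 30 residents per NH, 35 NHs per arm, 20% attrition, 1,000 residents per arm, contamination 5 to 10%.

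**The plan's own figure.** Two proportions, 24% v 16.8%, with continuity correction: 518 per arm, against 516 stated (491 without the correction). Design effect 1 + 29 × 0.02 = 1.58; 516 × 1.58 = 815; 815 / 0.8 = 1,019. The plan's 1,000 per arm is plausible.

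**Cost of leaving the strata out.** Let f be the share of between-NH variance that the strata explain. The SAP gives no f, so 0.25 and 0.50 are assumed. For m residents per NH:

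1. Variance the model without strata assumes: D0 = 1 + (m − 1) × 0.02.
2. True variance under stratified allocation: Df = 1 + (m − 1) × 0.02 × (1 − f).
3. Ratio of true to assumed standard error: r = √(Df / D0).
4. The test without strata behaves as if its critical value were 1.96 / r. Type I error = 2 × [1 − Φ(1.96 / r)].
5. Power with strata is the two-proportion power at n / Df. Power without strata = Φ(1.96 + z − 1.96 / r), where z is the normal quantile of the power with strata.

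Example, m = 30, n = 1,000, f = 0.50: D0 = 1.58, Df = 1.29, r = √(1.29 / 1.58) = 0.904, 1.96 / 0.904 = 2.169, type I error 0.030. Power with strata 0.941 (z = 1.564); without, Φ(1.96 + 1.564 − 2.169) = 0.912.

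Dilution by a fraction c moves the intervention rate to 0.168 + c × 0.072. The rows with m = 24 and n = 800 apply the 20% attrition to both cluster size and sample size. Losses are taken before rounding.

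| m, n per arm, dilution | f | Type I, strata out | Power, strata in | Power, strata out | Loss (points) |
|---|---|---|---|---|---|
| 30, 1,000, none | 0.25 | 0.040 | 0.916 | 0.900 | 1.6 |
| 30, 1,000, none | 0.50 | 0.030 | 0.941 | 0.912 | 2.9 |
| 24, 800, none | 0.25 | 0.041 | 0.870 | 0.852 | 1.8 |
| 24, 800, none | 0.50 | 0.033 | 0.897 | 0.863 | 3.5 |
| 24, 800, 5% | 0.25 | 0.041 | 0.832 | 0.810 | 2.1 |
| 24, 800, 5% | 0.50 | 0.033 | 0.863 | 0.821 | 4.2 |
| 24, 800, 10% | 0.25 | 0.041 | 0.788 | 0.763 | 2.5 |
| 24, 800, 10% | 0.50 | 0.033 | 0.822 | 0.773 | 4.9 |

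**Check by simulation.** 72 NHs, 4 strata, 4,000 runs per scenario, linear regression on NH proportions with and without strata, no dilution. This stands in for the mixed logistic model and does not fit it.

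| m | f | Type I, out / in | Power, out / in | Loss (points) |
|---|---|---|---|---|
| 30 | 0 | 0.046 / 0.047 | 0.888 / 0.887 | none |
| 30 | 0.25 | 0.034 / 0.043 | 0.905 / 0.926 | 2.1 |
| 30 | 0.50 | 0.028 / 0.046 | 0.921 / 0.953 | 3.2 |
| 24 | 0.25 | 0.044 / 0.053 | 0.848 / 0.875 | 2.8 |
| 24 | 0.50 | 0.029 / 0.049 | 0.859 / 0.901 | 4.2 |

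The Monte Carlo standard error of a 5% rejection rate is √(0.05 × 0.95 / 4,000) = 0.003, so the two methods agree. With f = 0, including the strata costs nothing measurable.

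**The case against.** The strongest reply is that this is a matter of efficiency, and a modest one. The test errs on the safe side, so no false-positive claim becomes more likely. Stratified allocation already delivers balance whether or not the model uses it. That stands, and it sets the size of the point.

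Four stronger readings are tempting, and the SAP does not support them:

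- **The omission takes the trial below 80% power.** With 800 analysed per arm, 30 per NH and 5% dilution, power is 77% at ICC 0.02, and 81% or 85% at residual ICC 0.015 or 0.010. A reader might take the gaps of 4 and 8 points as the cost. That treats the present design as unstratified, and so roughly doubles the loss in the simulation. The 77% also pairs a sample cut by 20% with an uncut cluster size; with 24 per NH it is about 80%. SAP 6.1 further keeps residents who leave after at least one month in the analysis, so most of the 20% is not lost from the denominator.
- **Baseline NPI, IADL and QOL-AD are ignored.** SAP 6.5.3 places these inclusion scores in the geriatric assessment done only in the intervention arm. Adjustment for a same-scale baseline is impossible. Inclusion GIR, age and Charlson index are held in both arms and could serve as covariates, but they would not correct for selective survival to the final visit. These endpoints are declared exploratory in 6.3.1.
- **The adjusted model in 6.2 is wrong to leave out prior admissions.** The data are collected ("Hospitalizations during the last 3 months by type of hospitalization (planned or in emergency) and by type of service"), but adding them is an optional covariate choice. Their absence is not an error.
- **Every secondary model is unadjusted.** The GIR model adjusts for its inclusion score.

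**Conclusion.** The confirmatory model does not reflect the stratified randomisation that the SAP itself reports. If the factors are prognostic, the test is conservative, with a type I error of about 0.03 to 0.04. It loses about 2 power points if they explain 25% of between-NH variance, and about 3 to 5 points if they explain 50%. Both shares are assumptions, and the result also rests on the plan's ICC of 0.02 and its cluster sizes. If the factors explain nothing, nothing is lost. Validity is not threatened: alpha is not inflated, and the SAP gives no basis for saying that this omission alone makes the trial underpowered. It is worth correcting because it concerns the one confirmatory test and the correction is essentially free.

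**What to change.** Before analysis:

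1. Add the randomisation stratification factors as fixed effects to the 6.1 model, and name them there.
2. Add them likewise to the mixed logistic and mixed linear models of 6.2 to 6.4. This does not extend to the test of NH incidence rates, the cumulative-incidence comparison or the centre-level t-test on staff burden, which are not specified as regression models.
3. Keep the arm-plus-centre model as a sensitivity analysis of the primary endpoint.
4. Optionally, adjust end-of-study NPI, IADL and QOL-AD for inclusion GIR, age and Charlson index. State that this is for precision and chance imbalance only, and does not address selective survival.

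The cost is a change of SAP wording. The factors were used at randomisation and are already to be described, and the covariates in item 4 are collected in both arms.

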## 6.2 Complementary analyzes of the primary endpoint

First, a second mixed logistic regression model will be used to study the effect of the intervention on the risk of admission to the ED in the first year, taking into account potential confounders of age, co-morbidities (Charlson), dependency (GIR score), antecedents of psychiatric pathologies and the presence of cognitive decline at inclusion. The effect of the intervention will be tested with a risk of 5% (exploratory test).

Then, in order to consider the differences in the duration of follow-up caused by the deaths and the anticipated stopping of study, other complementary analyzes will be conducted on the primary endpoint.

- Incidence rates defined as the number of emergency room admissions per 100 person-years (i.e. 100 persons followed exactly 1 year in NH) will be calculated for each NH and a statistical test will be performed to determine if the difference between the incidence rates in both groups is significant (exploratory test at 5%). To calculate incidence rates, the at-risk follow-up time for each subject will first be calculated as the time in years between the start date of follow-up (i.e. end date of inclusions in the center) and the date of point (i.e. start date of follow-up plus 1 year) or the date of premature dropout of the study for the subjects who stopped the study before 1 year of follow-up MINUS possible durations of hospitalization (i.e. the subjects are no longer at risk of transfer to the ED

|                    |                                                                   |                                                                                                            |
|--------------------|-------------------------------------------------------------------|------------------------------------------------------------------------------------------------------------|
| Principal analysis | Statistical Analysis Plan (SAP)-IDEM Study 0910701
Version 1.0 | [figure not shown]
Hôpitaux de Toulouse |
|                    |                                                                   | 07/22/2016                                                                                                 |

when they are hospitalized). Then, for each subject, the number of transfer to ED that occurred during the risk period will be counted. The incidence rate for each NH will be calculated as the total number of ED transfers divided by the sum of the at-risk follow-up times for the center's subjects and will be transformed per 100 person-years.

- Finally, a survival analysis will be carried out to study the delays until the occurrence of the event (i.e. first transfer to the ED). In this study, death is a competitive risk to consider in the analysis given that the risk of having an event after death is zero (i.e., no independence between the two risks). Standard Kaplan-Meier survival analyzes do not lead to valid results for a specific risk if failures for another cause are treated as censorship. A suitable method is the use of cumulative impact functions that represent the cumulative probability of failure due to a specific cause over time. Cumulative incidence functions will be calculated for each group considering the death as a competitive risk and the difference between the functions of the 2 groups and the 5% Alpha risk method will be tested (exploratory test). Cumulative incidence rates estimated at 1 year will be presented for each group with their 95% confidence interval. Deadlines will be calculated in days between the start date of follow-up and:
  - the date of first ED transfer for the subjects having had the event studied in the year or
  - the date of death for subjects who died in the year (subjects with competitive risk) or
  - the premature dropout date of the study if dropped out for a reason other than death before one year (censored subjects) or
  - the point date for the remaining subjects who will also be censored (i.e. end date of inclusions in the center plus 1 year)

Population of analysis: All complementary analyzes of the primary endpoint will be performed on the ITT population. The analysis of incidence rates will also be performed on the PP1 population.

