### 6.3.2 ED transfer during 18 months

The first admission to an ED within 18 months of the start of the follow-up will be the event considered.

The main analysis (logistic regression with random effects) and the additional analyzes planned on the main judgment criterion will be carried out again considering this time 18 months of follow-up for each subject.

To calculate incidence rates, the risk follow-up time for each subject will be the time in years between the start date of follow-up (i.e. end date of inclusions in the center) and the date of point (i.e. start date follow-up plus 18 months) or the premature dropout date of the study for subjects who stopped the study before 18 months of follow-up MINUS possible hospitalization times.

For the survival analysis, the time will be calculated in days between the start date of follow-up and:

- the date of first hospitalization in the emergency department for subjects having had the event studied within 18 months or
- the date of death for the subjects who died within 18 months without having gone to the ED beforehand (subject with competitive risk) or
- the premature dropout date of the study if dropped out for any reason other than death within 18 months (censored subjects) or

|                    |                                                                   |                                                                                                            |
|--------------------|-------------------------------------------------------------------|------------------------------------------------------------------------------------------------------------|
| Principal analysis | Statistical Analysis Plan (SAP)-IDEM Study 0910701
Version 1.0 | [figure not shown]
Hôpitaux de Toulouse |
|                    |                                                                   | 07/22/2016                                                                                                 |

- the date of the point for the remaining subjects who will also be censored (i.e. end date of the inclusions in the center plus 18 months)

Population of analysis: The main analysis will be carried out on the population ITT as well as on the populations PP1 and PP2. The additional analyzes will be done on the ITT, the analysis of the incidence rates will also be carried out on the PP1 and PP2 populations.

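### The exploratory adjusted ED-transfer model leaves out recent hospitalization, the closest baseline proxy for the endpoint, although it is recorded in both arms; adding it is cheap and the expected benefit modest.

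*SAP*

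**What the plan says.** SAP 6.2 plans a second mixed logistic model for ED admission in the first year, "taking into account potential confounders of age, co-morbidities (Charlson), dependency (GIR score), antecedents of psychiatric pathologies". The list ends with "antecedents of psychiatric pathologies and the presence of cognitive decline at inclusion", so there are five covariates and none concerns earlier hospital use. The model's status is explicit: "The effect of the intervention will be tested with a risk of 5% (exploratory test"). The confirmatory model in 6.1 has only randomization group as a fixed effect and center as a random effect.

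SAP 6.3.2 carries the covariate list over to the longer follow-up: "the additional analyzes planned on the main judgment criterion will be carried out again considering this time 18 months of follow-up".

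Among the inclusion data, SAP 6.5.3 lists "Hospitalizations during the last 3 months by type of hospitalization (planned or in emergency) and by type of service". It stands under characteristics that "will be described for the entire analysis population and will be described in the 2 groups (intervention, control"). A separate list covers what only one arm has: "The following results from the Comprehensive Geriatric Assessment (CGA) obtained during the inclusion visit only for the intervention group". Recent hospitalization is not on that second list. Under 6.5.1 the descriptive tables carry no between-group tests, and no other section brings prior hospitalization into a model of ED transfer.

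**The concern.** The adjusted model exists to account for confounders of the ED comparison. Age, Charlson, GIR, psychiatric history and cognitive decline are indirect markers of ED risk, whereas a recent emergency stay is a direct one. It precedes follow-up, which under 6.1 starts at the end of the center's inclusion wave. It comes from the inclusion data common to both arms and not from the intervention-only geriatric assessment. Adjusting for it is therefore feasible and raises no problem of conditioning on a consequence of treatment. The SAP gives no reason for omitting it.

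If the arms differ in recent emergency use, the listed covariates may remove only part of that difference, and the plan has no prespecified way to deal with the rest. Section 2 states that the analysis will not be blind, so adding the covariate after an imbalance is seen would be an unblinded, post hoc choice. Section 1 says that analysis begins only after the plan is validated, which is the point at which the list can be fixed.

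**Working it through.** **Comparing the lists.** The 6.2 list (age, Charlson, GIR, psychiatric history, cognitive decline) and the both-arm baseline list in 6.5.3 differ on recent hospitalization: it is in the second and absent from the first. The omission and the availability of the data are both confirmed.

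**Inputs from SAP 3.3.**
- Among residents meeting the IDEM criteria, "12% were admitted to hospital services in 3 months". The plan's chain reproduces: 4 × 12% = 48% a year; half via ED = 24%; 24% × 0.70 = 16.8%; planned difference 24 − 16.8 = 7.2 points.
- The 516 per group reproduces as 518 (two-sided 5%, 80% power, continuity-corrected). It does not depend on the adjusted model, and neither do the later figures of 950 to 1,050 and 1,000 per group.
- Residents per arm 1,000; about 30 per home; ICC 0.02.
- Prevalence of a recent admission via the ED: p = 0.12 × 0.5 = 0.06.

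**Assumptions, not in the SAP.** The ICC of 0.02 also applies to this baseline item. A recent emergency stay multiplies one-year ED risk by RR = 2 (range 1.5 to 3).

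**Step 1: chance imbalance between arms.**
Design effect = 1 + (30 − 1) × 0.02 = 1.58.
SD = √[2 × 0.06 × 0.94 / 1,000 × 1.58] = 0.01335, about 1.3 points.

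**Step 2: risk r in residents without a recent stay.** Setting 0.24 = r[1 + 0.06(RR − 1)] gives:
- RR 1.5: r = 0.24/1.03 = 0.233
- RR 2: r = 0.24/1.06 = 0.226
- RR 3: r = 0.24/1.12 = 0.214

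**Step 3: shift in the risk difference for a 1-SD imbalance.** Shift = 0.01335 × r × (RR − 1).

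| RR | Shift (points) | Share of 7.2 points |
|---|---|---|
| 1.5 | 0.16 | 2% |
| 2 | 0.30 | 4% |
| 3 | 0.57 | 8% |

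**Step 4: a larger imbalance.** At 4 points and RR 2 the shift is 0.04 × 0.226 = 0.9 points (0.5 to 1.7 for RR 1.5 to 3), or 13% (6 to 24%) of 7.2. But 4/1.335 = 3.0 SD, so chance alone would rarely produce it.

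**Step 5: odds-ratio scale.** With an assumed odds ratio of 1.5 to 4 for the covariate and an imbalance of 1 to 4 points, the crude risk shifts by 0.1 to 1.2 points, a spurious odds ratio of 1.004 to 1.07.

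**Step 6: precision.** Variance explained = 0.06 × 0.94 × [r(RR − 1)]² / (0.24 × 0.76) = 1.6% at RR 2 (0.4% at 1.5, 5.7% at 3). The gain is small.

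Steps 3 to 5 give crude shifts. They make no allowance for the part of an imbalance that the five existing covariates would absorb.

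**The case against.** The strongest reply is that this is a choice of covariates and not an error. The plan prespecifies five plausible confounders in a model it labels exploratory, promises nothing about prior hospital use, and contradicts nothing by leaving it out. Almost any list could take one more predictor. That stands, and it limits the weight of the point. What remains is that this variable is nearest to the endpoint and is already collected.

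Three further replies also stand.
- The variable is a proxy. The endpoint in 4.1 is ED admission over one year. An emergency hospitalization can also be a direct admission to another ward, which 4.3 treats as a separate endpoint. The SAP summary allows a two-month inclusion interval per home, so the 3-month look-back need not adjoin follow-up.
- The existing covariates may be correlated with recent hospitalization and so remove part of any difference.
- The 6.5.3 table will show the variable by group, so an imbalance would be visible to the reader.

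A reader might infer that a real case-mix difference is being left uncorrected. The SAP shows no such difference. Homes are randomized 1:1, and the summary says the randomization takes type of institution and type of resident into account. Selection after randomization is possible: the physician conducting the inclusion visit carries out the geriatric assessment in the intervention arm only and so knows the arm, and eligibility involves judgments such as life expectancy. That is a possibility and not evidence.

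A reader might also want to adjust for a no-transfer or no-hospitalization directive on file at inclusion. The SAP does not support this. It gives no prevalence or effect for such directives, and equating the anticipated prescriptions in 6.5.3 with the ten-item list in 4.2 g is an inference. The intervention-arm physicians are trained beforehand and advance directives are among the intervention's aims, so the SAP does not show that their recording at inclusion is free of influence from assignment.

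**Conclusion.** The omission is real and easily remedied, and its expected effect is modest. It touches only the exploratory adjusted model at 12 months and its 18-month repeat. The confirmatory result and the sample size are unaffected. Under chance imbalance the expected shift is about 0.3 points (0.16 to 0.57), or 4% (2 to 8%) of the planned 7.2 points. This rests on the SAP's 12% and one-half, on applying the ICC of 0.02 to this covariate, and on an assumed risk ratio of 2 (1.5 to 3). A materially larger effect would need selective recruitment after randomization, which the SAP neither shows nor excludes. The case for changing the list is that the data are in hand and a prespecified covariate is credible, while one added after unblinded results is not.

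**What to change.** Before analysis starts, add one covariate to the 6.2 adjusted model, at 12 months and in the 18-month repeat under 6.3.2: at least one emergency hospitalization (including ED) in the 3 months before inclusion, yes/no. Leave the 6.1 model and the other five covariates unchanged. Do not add a directive-on-file covariate. If the sponsor prefers the present list, state the reason in 6.2.

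The cost is one line of SAP text and one more fixed effect with about 2,000 residents; 6.5.3 shows that the item is already collected. The small downside is that section 7 applies no imputation, so residents missing this item drop out of the adjusted model. Their number by arm should be reported with the result.
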